## Abstract

**Background:**

Language barriers play a decisive role in determining the outcomes of medical consultations between healthcare providers and their foreign patients. This issue is a significant challenge to the German healthcare system, especially with the rising number of refugees in recent years. The communication gap between healthcare professionals and their non-German speaking patients sometimes leads to unnecessary medical re-admission, insufficient medical history, incorrect diagnosis, and treatment plans. In this study, we aim to assess the usability and accuracy of a novel digital translation tool in collecting medical history from patients in their native language and to check its effects on healthcare outcomes.

**Methods:**

The study aims to monitor the implementation of a new digital communication assistance tool (DCAT) and to investigate its impact on the mutual understanding between refugee patients and their German general practitioners (GPs). In the first study phase, an action-oriented approach is used to implement DCAT. In the second study phase, DCAT use will be evaluated with a mixed methods design.

The main outcome assesses the re-consultation rates of patients before and after using DCAT. Secondary outcomes include the usability of the tool, its acceptance and perceived quality by patients, the accuracy of the information collected as determined from analysing the reasons for the consultation (ICPC-2 codes), and diagnosis (ICD-10 codes). The acceptance by patients, socio-demographic factors and native language are also taken into account.

The research designs for both study phases include questionnaires, semi-structured interviews, non-participant observation and analysis of collected patients’ data.

All the collected data is pseudonymised.

**Discussion:**

The DCAT study is one of the new research projects in primary healthcare investigating the usability, accuracy, and acceptance of digital translation tools during medical encounters. We aim to eliminate significant communication errors and misunderstandings in medical consultations, thereby improving the quality of healthcare outcomes. By applying an action research design, we will attain a more comprehensive evaluation of DCAT scopes and limits. The results of this study are expected to give an in-depth understanding of possible applications and benefits of digital translation tools for patient care.

**Trial registration:**

German Clinical Trials Register DRKS00013076, 29/09/2017.

**Electronic supplementary material:**

The online version of this article (10.1186/s12913-019-3928-1) contains supplementary material, which is available to authorized users.

## Background

Over one million refugees and asylum seekers have been registered in Germany within the last three years [1]. The German healthcare system faces considerable difficulties in providing adequate and high-quality healthcare for such a large number of people [2, 3]. Many factors influence the provision of healthcare to this group of patients, and some of the most important arise from language and cultural barriers [4]. These problems also contribute to the lack of patient knowledge of the German healthcare system [5, 6].

In most cases, healthcare professionals cannot rely on the accuracy of the medical history collected from refugees and asylum seekers due to the limited access to professional interpreters [7]. This also increases the risks of medical errors and misdiagnosis received by these patients as well as potential drug-related adverse effects and medical complications [8, 9]. While professional interpreters are usually not available for such a large number of patients, especially in rural areas [6], health policymakers generally prefer not to employ interpreter-services because of the financial burden this also places on the healthcare system [10] and the German public health insurance does not typically cover such expenses [11]. Additional concerns relating to the use of professional interpreters include privacy and patient-physician confidentiality as well as the interpretation quality for medical purposes [12].

The problem of language barriers in the German healthcare system has been appreciated for some time, but adequate practical solutions have not been forthcoming [2]. Digital approaches may bridge the communication gap during medical consultations and address the needs of both patients and healthcare providers correctly, especially when an interpreter is not available and there is a need for essential communication, i.e. in a spontaneous consultation.

There have been attempts to develop such digital tools. However, the quality and feasibility of these approaches have rarely been examined methodologically in a clinical context [13]. Whereas earlier tools focused mostly on self-diagnosis and treatment in the absence of healthcare professionals [8], this interventinon seeks to assist healthcare providers by collecting medical histories from the non-German speaking patients and then provide them with the collected relevant medical information in the German language. The primary goal of the DCAT is, therefore, to collect structured medical histories from non-German speaking patients in their native language and then to provide physicians with a corresponding German medical report to aid in patient primary care.

### The aim of the study

In this study, we explore DCATs usability, accuracy and the helpfulness as well as its impact on patient’s utilisation of medical services (re-consultations). By doing so, perspectives from all stakeholders (GPs, refugee patients and healthcare system insurers/providers) are taken into account.

The results of this study are expected to indicate the effectiveness of DCAT with respect to improving the communication with medical professionals and consequently medical outcomes for non-German speaking patients of the healthcare encounter. The study is located at a refugee camp in Lower Saxony in Germany. A daily GPs consultation hour at a primary healthcare centre in the camp is offered for acute medical conditions for all camp residents.

## Methods

### Design

The first study phase follows an action-oriented approach, meaning that observation outcomes can be used as an input to improve the content and implementation process of DCAT. This pragmatic approach allows us to make adjustments within a complex intervention in a barely known field, in response to unexpected problems and new opportunities that arise throughout the study. In contrast to other interventional procedures, the action research method requires close collaboration between researchers and other involved parties in the field [14, 15]. This approach also has proved its validity in evaluating health-related issues among refugees and asylum seekers [16, 17]. The “action” follows a circular process consisting of planning, implementation, observation and reflection, which is repeated several times. Since it is not possible to ascertain which challenges may be faced during the testing, it is difficult to determine ahead of time the duration of the action research method. This initial study phase ends with a successful three week preliminary testing with patients supported by intensive field observation and technical backup. Following this testing, the final version of DCAT will be fixed and will remain unchanged during the second study phase.

For a better understanding of DCAT impact, potential and limitations, a mixed methods research design is to be combined with quantitative and qualitative research methods in the second study phase [18, 19]. The quantitative approach includes DCAT-users and non-DCAT users and therefore offers the possibility to compare both groups in an interventional study design.

The primary outcome will be the consultation rate of patients who used DCAT compared with those who did not use this digital translation tool. As we found in a previous pilot study, the consultation rate of refugee patients at the primary healthcare centre is higher, especially compared to the non-refugee population, and this might be a result of miscommunication. Also, consultation rates are key values for healthcare costs.

As a secondary outcome, the following are to be assessed:The perceived quality of the communication in the consultation by both patients and healthcare professionals. After each consultation patients are asked to fill in questionnaires about their perceptions around mutual understanding with the attending physician.The perception of the usability and acceptance of the tool by patients and GPs, which is also gauged through questionnaires after each consultation.The usability and acceptance of DCAT by different patient subgroups according to age, gender, country of origin, asylum status, educational level and spoken languages. When patients decide to stop using DCAT, this will also be registered.The accuracy of collected information through DCAT. The aim is to clarify whether DCAT can be reliably utilised and incorporated into the clinical decision-making process to improve healthcare outcomes [20, 21]. DCAT estimates the reasons for the encounter as ICPC-2 codes based on the information provided by the patient, and doctors will also be indicating their diagnosis (ICD-10 codes). We want to compare the DCATs estimated reasons for a consultation and the GP’s diagnosis in terms of plausibility and contingency to investigate the accuracy of the provided medical information by DCAT [22]. Also, GPs will be asked after each consultation through questionnaires if their impression of the patient’s description contradicts the information provided by DCAT.

For a deeper insight into the acceptance of DCAT users, we will apply qualitative research methods, namely:Use of open and partially standardised interviews conducted with healthcare workers (GPs and nurses) and a group of selected patients in the refugee camp.The researchers also will explore the use of DCAT as a non-participant observer.

The research design of the DCAT Study is shown in Fig. 1.

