### Sample size calculation

The sample size calculation is based on the average numbers of patients in the last 12 months in Friedland. Due to fluctuations in refugee flows (ranging from 285 to 636/month), it is difficult to predict how many patients will be treated at the primary healthcare centre during the study period and meet the inclusion criteria, especially regarding the available languages. Despite these uncertainties, during the six months recruitment period we aim to include a total sample size of 880 participants (study group: 440 patients using DCAT, 440 patients not using DCAT). The sample size calculation is based on the consultation rates for medical treatment at the primary healthcare centre in Friedland as this is the primary outcome of the study protocol. Our previous research in the preparation phase revealed an average consultation rate for medical treatment of 2.65 (SD: 3.44) consultations per patient. Assuming a 10% dropout rate, to measure a minimal difference of 0.65 consultations per patient, 5% significance (two-sided) and a standard deviation of 3.5, 20 patients should be recruited per week to use DCAT to achieve the identified sample target.

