**Age, gender, asylum status, and affiliation to a language group**

Initially, patients using DCAT select their native language or dialect. This selection then directs further audio and visual information. Patient age, nationality, asylum status, sex are also extracted from the patient’s note.

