**Acceptance, usability, quality of communication, accuracy of DCAT information, and presence of ad-hoc (lay) interpreters**

When a patient finishes entering his/her data on DCAT, a digital questionnaire follows to assess patients’ experiences with DCAT (see Additional file 1). This questionnaire consists of two parts, the first consists of four questions and is applied directly after using DCAT. These questions seek to evaluate the acceptance and usability of DCAT. The final question regards the educational level of the patients.

The second section of the patient questionnaire follows after the consultation. It has five questions, which focus on the impact of using DCAT in the consultation situation, especially the communication and mutual understanding between the healthcare providers and the patients.

The attending physicians at the Friedland primary healthcare centre are asked to give their feedback on each consultation also using a two-part questionnaire (see Additional file 2). The first section comprises three questions, which ask the doctors their opinions on the perceived quality of communication and mutual understanding throughout the consultation. Whether ad-hoc interpreters are present is also documented. The second set of questions follows only when a medical report (synopsis) is produced through DCAT (see Additional file 3) and asks whether this printed report influences the consultation. Also, any inconsistencies between the DCAT collected information and clinical impressions of the doctors are sought.

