It should be noted however that DCAT is neither able to make a diagnosis nor can it give medical advice. It is an aid for doctors to obtain the medical history (symptoms and signs) from the patient perspective without the need for interpreters and translators.

We do expect some possible challenges with our study design. As this digital communication assistance tool is newly developed and its adoption will likely change the daily routine at the medical consultation, we are expecting some reluctance to use it, especially on the part of the healthcare provider. Such potential difficulties may require additional DCAT revisions during the study to ensure the quantitative as well as qualitative research goals (extension of the initial 18 month study period, changing the locations, where the patient can use DCAT, changing routine, e.g. admission times).

We also anticipate that not all patients will utilise DCAT because of unfamiliarity with the technology involved or the unavailability of some spoken languages at the primary healthcare centre in Friedland. During the study period, we will find out about such possible limitations and obstacles that might prevent DCAT usability.

In conclusion, this study remains an essential step to assess the potential effectiveness of the DCAT tool in facilitating communication and removing language barriers to improve the quality of the healthcare encounter for patients who do not speak German.

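### Subgroup acceptance of DCAT is asked only of patients who finish an entry, so a subgroup that mostly declines the tool can score as high as any other

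*Protocol article*

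**What the plan says.** All references are to the protocol article.

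- **Objective.** Methods, Design, lists among the secondary outcomes "The usability and acceptance of DCAT by different patient subgroups according to age, gender, country of origin, asylum status, educational level and spoken languages". It adds that a patient's decision to stop using the tool is registered.
- **Instrument.** The measurement section on acceptance and usability says "When a patient finishes entering his/her data on DCAT, a digital questionnaire follows". Of its first part it says "These questions seek to evaluate the acceptance and usability of DCAT". The second part follows the consultation and concerns the effect of having used DCAT.
- **Voluntary use.** Recruitment and informed consent leaves both study participation and use of the tool to the patient.
- **Expected non-use.** The Discussion says "We also anticipate that not all patients will utilise DCAT because of unfamiliarity with the technology involved", or because a language is not available. It adds that the study will learn about such obstacles.
- **Sources for the subgroup factors.** For language: "Initially, patients using DCAT select their native language or dialect". For four others: "Patient age, nationality, asylum status, sex are also extracted from" the patient notes. For education, in the DCAT questionnaire: "The final question regards the educational level of the patients".
- **Sample.** The recruitment aim is given as "study group: 440 patients using DCAT, 440 patients not using DCAT". It is derived for the consultation-rate comparison.

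**The concern.** The objective asks how well different kinds of patient accept the tool. The instrument is answered only by patients who agreed to use it, started it and finished. If reluctance differs by age, education or origin, the reluctant members of a subgroup drop out before the question is put, and the subgroup is represented by its most willing members.

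The Discussion itself names unfamiliarity with the technology as a reason for non-use, which may plausibly vary by age and education. At stake is a conclusion that acceptance is similar across subgroups when one of them largely does not use the tool. That would mislead anyone deciding where DCAT could stand in for an interpreter.

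**Working it through.** **1. Who is visible at each step**

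| Step | Recorded in the text? |
|---|---|
| Offered DCAT | no count described |
| Declined, never started | no count described |
| Started, then stopped | yes, stopping is registered |
| Finished an entry | yes, acceptance questionnaire follows |

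A patient who never starts cannot be registered as stopping, so the stopping record does not close the gap.

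**2. The plan's own figure**

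The only planning figure that enters is 440:440. With n = 2(1.960 + 0.842)² × SD² / 0.65² per group and an assumed power of 80% (none is stated):

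- SD 3.5 gives 456, and 456 / 0.90 = 507 after 10% dropout.
- SD 3.44 without dropout inflation gives 440.

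The stated inputs thus do not reproduce 440 at that power. This is a separate matter and does not affect the present point. What matters here is only that the split is a 1:1 target.

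**3. What the questionnaire can and cannot show**

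Assumptions, none of them in the document: two subgroups of 440 patients each are offered DCAT, uptake is u in A and 1 − u in B, and 85% of users in each find it acceptable. Decliners count as not accepting.

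- Users: 440u and 440(1 − u), always 440 users and 440 non-users in total.
- Questionnaire result: 85% in each subgroup, whatever u is.
- Acceptance among those offered: 0.85u and 0.85(1 − u).

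| u in A / B | Users A / B | Questionnaire A v B | Among offered A v B |
|---|---|---|---|
| 0.5 / 0.5 | 220 / 220 | 85% v 85% | 42.5% v 42.5% |
| 0.6 / 0.4 | 264 / 176 | 85% v 85% | 51% v 34% |
| 0.8 / 0.2 | 352 / 88 | 85% v 85% | 68% v 17% |
| 0.9 / 0.1 | 396 / 44 | 85% v 85% | 76.5% v 8.5% |

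The questionnaire column does not move, although the last column runs from no difference to a ninefold one.

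**4. What the 1:1 target hides**

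The overall use share in the sample is 440 / 880 = 50% by design, so it says nothing about absolute uptake. Relative uptake is different. At u = 0.8 / 0.2 the user/non-user counts are 352/88 in A and 88/352 in B, an odds ratio of (352/88) / (88/352) = 4 / 0.25 = 16. That contrast stays visible, provided the non-users are eligible patients from the same period and were not selected by the subgroup factor. The article does not say how non-users arise.

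**5. Which factors can be recovered**

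Age, sex, nationality and asylum status come from the patient notes, and every presentation at the centre is registered, so uptake by these four can be counted without DCAT use. Language is chosen inside DCAT and education is asked in its questionnaire. For these two, no source for non-users is named.

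**The case against.** The strongest reply has four parts.

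- **Use is visible elsewhere.** GPs give feedback on each consultation, with a second part only when a DCAT report exists, so use and non-use can be told apart. Interviews, observation and staff comments may also reveal obstacles. This stands, and it is why the fix is cheap. But none of it is tied to the subgroup acceptance outcome, and the Design section presents the qualitative work as insight into the acceptance of users.
- **This is a condensed article.** Logs of offers and the reporting denominator may sit in the full protocol or analysis plan. That is fair for the details. The point rests on what the article does state: when the acceptance questions are put, and to whom.
- **The quota.** A reader might infer that 440:440 conceals uptake altogether. The document does not support that. The split is an aim, stated amid uncertainty about patient numbers, and it removes only absolute uptake from view (step 4).
- **The patient flow.** A reader might multiply the stated 285 to 636 per month by six, get 1,710 to 3,816, and infer that most patients declined. That does not follow. The article calls these refugee flows and says it is uncertain how many will be treated and meet the inclusion criteria, especially on language. People who are ineligible or never offered DCAT are not decliners. For the same reason, dividing users by everyone in the register would make a missing language look like rejection.

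**Conclusion.** The point holds in limited form. As described, the subgroup outcome measures acceptance among patients who voluntarily completed DCAT, and equal scores across subgroups are compatible with very unequal uptake. In the illustration, 85% against 85% goes with anything from 42.5% against 42.5% to 76.5% against 8.5% among those offered. The true size is unknown: the article gives no uptake rates, and the illustration assumes equal ratings among users and counts every decliner as not accepting.

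The gap can be repaired from records the centre already holds for four of the six factors, but not for education, and only approximately for language. It affects a secondary outcome, not the consultation-rate comparison, and is best treated as a cheap improvement.

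**What to change.** 1. Make uptake a component of acceptance: DCAT users divided by patients who presented at the centre in the recruitment period and are eligible by language, approximated by nationality where language is not recorded. Where offers are logged, use patients offered DCAT as the denominator. Count patients rather than visits.
2. Report uptake by age, sex, nationality and asylum status from the register and patient notes.
3. Show it beside the questionnaire result, labelled *acceptance among patients who completed DCAT*.
4. Limit conclusions on educational level and language to users, unless a brief log of offers and refusals records these two factors.

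The cost is some extra counting and a language denominator that is only approximate. Since written consent is described for patients willing to take part, the study team should confirm that aggregate counts of patients who declined are covered by its consent and data-protection arrangements.

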**Reasons for Consultations and Diagnosis**

DCAT encodes automatically the estimated consultation reason as ICPC-2 code based on a patient’s input data [26, 27]. Diagnoses are documented afterwards from the patient notes made by the primary healthcare doctors. These are regularly kept for documentation purposes in the primary healthcare centre in Friedland.

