### Data management

Every patient in the DCAT study will receive a unique digital readable label (QR-Code), which is placed on his/her identification card (ID) in order to pseudonymise patient’s data. The social service workers issue these IDs to all refugees and asylum seekers after their arrival to Friedland. DCAT is launched after scanning the QR-Code. Therefore, the printed report, which has the QR-Code, can only be reassigned back to the patient by medical staff at the primary healthcare centre. Thus in case a report is lost, no one can identify it, which safeguards the patient’s personal as well as medical data.

Personal information allowing patient identification (e.g. first and last name) is not collected by DCAT. The collected data is not shared with other authorities or third parties. All other information not described above, e.g. health-related information given by the patient through DCAT is deleted permanently. The pseudonymised patient notes are evaluated by the research team and coded according to diagnosis (ICD-10 codes) [22].

All quantitative and qualitative data is only accessible by the study team. The study team is familiar with data privacy regulations and committed to data protection principles. A data monitoring committee is not needed in this trial because of the relatively short study period and the minimal risks to patient safety using the DCAT in comparison to randomised controlled trials on drugs and biologics.

All collected data will be permanently deleted ten years after the study.

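### DCAT's accuracy is judged against a GP diagnosis made with the DCAT report available, so the comparison shows concordance and cannot establish accuracy or reliability for decisions

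*Protocol article*

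**What the plan says.** Accuracy of the collected information is a secondary outcome. The Abstract says it is determined from the ICPC-2 reasons and the ICD-10 diagnoses. The Design section states the purpose: "The aim is to clarify whether DCAT can be reliably utilised and incorporated into the clinical decision-making process to improve healthcare outcomes". It then compares DCAT's estimated reasons with the GP's diagnosis "in terms of plausibility and contingency to investigate the accuracy of the provided medical information by DCAT".

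On the tool's side, under Reasons for Consultations and Diagnosis: "DCAT encodes automatically the estimated consultation reason as ICPC-2 code based on a patient’s input data". On the GP's side, the same section has diagnoses documented afterwards from the notes the doctors keep.

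Two places show that the GP has the tool's output. The Background gives DCAT's primary goal as collecting histories in the native language and then "to provide physicians with a corresponding German medical report to aid in patient primary care". Where a report has been produced, the second part of the GP questionnaire "asks whether this printed report influences the consultation". GPs are also asked whether their own impression contradicts the DCAT information.

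**The concern.** A reference standard should be formed without knowledge of the test it judges. Here the diagnosis is made with the test's report available. If a wrong report shapes the diagnosis, the consultation is scored as agreement, and such an error would matter most for a tool meant to support decisions.

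The setting makes this plausible. The Background says that interpreters are scarce and that histories from these patients often cannot be relied on, and the Discussion presents DCAT as a way to take a history without an interpreter. A GP may therefore have little other history to set against the report.

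The two codes also describe different things. A reason for encounter is what the patient comes with, and a diagnosis is what the GP concludes. A correctly captured symptom may not line up with the final diagnosis. Neither high nor low agreement would then answer the question the Design section asks.

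**Working it through.** The article gives no expected agreement, statistic or threshold for this outcome, so there is no planned figure to reproduce. The check traces the comparison through the text, then illustrates the possible size with assumed values.

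**Tracing the comparison**

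1. Measure under test: an ICPC-2 reason, generated by DCAT from the patient's entries (Reasons for Consultations and Diagnosis).
2. Access: the German report goes to the physician as an aid (Background, Discussion), and GPs are asked about its influence on the consultation (Acceptance, usability section). The article does not say that the ICPC-2 code itself is shown to the GP. The dependence runs through the report's content.
3. Reference: the GP's diagnosis, documented afterwards from the notes.
4. Use: the two are compared to judge accuracy and reliability for decisions (Abstract, Design).
5. Other check: the GP contradiction item. It sets the patient's description against the DCAT information, so it compares like with like, but the GP answers it knowing the report.

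No section describes a history or diagnosis obtained without the report.

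**Possible upward shift (all values assumed)**

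Let a be the agreement with an independent reference, and f the share of otherwise discordant consultations in which the GP's diagnosis follows the report.

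Observed agreement = a + f(1 − a)

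| a | f = 10% | f = 25% | f = 50% |
|---|---|---|---|
| 50% | 55% | 62.5% | 75% |
| 60% | 64% | 70% | 80% |
| 70% | 73% | 77.5% | 85% |

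For example, 0.60 + 0.25 × 0.40 = 0.70. Over this grid the shift runs from 3 to 25 percentage points, and it is zero if f = 0.

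Correcting for chance does not remove the shift. With 10 equally frequent categories (assumed), chance agreement is 0.10. At a = 0.50, kappa is (0.50 − 0.10)/0.90 = 0.44. With f = 0.50 it becomes (0.75 − 0.10)/0.90 = 0.72.

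**Possible downward shift**

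Let m be the share of truly agreeing consultations scored as discordant only because a reason is set against a diagnosis.

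Observed agreement = a(1 − m) + f(1 − a)

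The two effects cancel when m = f(1 − a)/a. At a = 0.60 this is 0.10/0.60 = 16.7% for f = 25%, and 0.20/0.60 = 33.3% for f = 50%. Above those values of m, observed agreement falls below a. The planned data identify neither f nor m. The report-influence item does not measure f, because it asks about the consultation and not about adopting the report's reason in an otherwise discordant case.

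**The case against.** The strongest reply is that the GP is no passive reader of the report. The GP sees the patient, an ad-hoc interpreter may be present, and a contradiction can be recorded. A misleading report counts as agreement only if it goes unnoticed and the diagnosis follows it. The criterion is plausibility, not an exact match, so a headache followed by a migraine diagnosis could count as consistent. The outcome is secondary, the article speaks of exploring accuracy, and the Discussion says that DCAT does not diagnose.

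Most of this stands, and it rules out several stronger readings that a reader might infer:

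- *That agreement is inflated, or measures only how far GPs follow the report.* The effects pull both ways, and the GP has other information.
- *That coders are unmasked.* The article is silent, and silence in a condensed article is no finding.
- *That the text contradicts itself on who assigns ICD-10 codes.* Design has doctors indicating the diagnosis, and Data management has the research team coding from notes. These can be read together, since diagnoses are documented from the doctors' notes.
- *That the contradiction item could serve as the main accuracy measure.* It is answered with the report known, so it is not independent either.

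The reply does not supply an independent reference. A plausibility criterion may reduce the mismatch between reason and diagnosis, but it leaves the GP's exposure to the report as it is.

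**Conclusion.** The point holds in a limited form. The diagnosis used to judge DCAT is made with DCAT's report available, and no report-free reference is described. The comparison can therefore show concordance in use, but it cannot establish accuracy or reliability for clinical decisions. This follows from what the article states and does not depend on details left to a fuller document.

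The size and net direction of the bias are unknown. The upward shift of 3 to 25 points rests wholly on assumed a and f, and a mismatch between reason and diagnosis could cancel or reverse it. The primary outcome, the consultation rate, is untouched. The point should be acted on because accuracy is among the study's stated aims and the conclusion attached to it goes beyond what the comparison can carry.

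**What to change.** In the Abstract and the Design section, call this outcome *concordance of the DCAT reason for encounter with the GP diagnosis*, and do not draw the reliability-for-decisions conclusion from it.

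The research team already codes ICD-10 from the notes (Data management). State that they do so without sight of the DCAT code. This removes a second possible source of dependence but does not undo the GP's knowledge of the report, so the new label is needed in any case.

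Report concordance with a 95% CI overall. Report it descriptively by the GP's answer on report influence (available where a report was produced) and by presence of an ad-hoc interpreter. Both items are already collected. Set the GP contradiction item beside it as a like-for-like check that is also not independent.

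The cost is a less favourable label than accuracy and slightly more analysis work. No new data are needed. Masking should add little, assuming the notes can be given to the coders without the DCAT code, which the article does not describe.
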